## Abstract

**Introduction:**

The development of malignant pleural effusion (MPE) results in disabling breathlessness, pain and reduced physical capability with treatment a palliative strategy. Ambulatory management of MPE has the potential to improve quality of life (QoL). The OPTIMUM trial is designed to determine whether full outpatient management of MPE with an indwelling pleural catheter (IPC) and pleurodesis improves QoL compared with traditional inpatient care with a chest drain and talc pleurodesis. OPTIMUM is currently open for any centres interested in collaborating in this study.

**Methods and analysis:**

OPTIMUM is a multicentre non-blinded randomised controlled trial. Patients with a diagnosis of MPE will be identified and screened for eligibility. Consenting participants will be randomised 1:1 either to an outpatient ambulatory pathway using IPCs and talc pleurodesis or standard inpatient treatment with chest drain and talc pleurodesis as per British Thoracic Society guidelines. The primary outcome measure is global health-related QoL at 30 days measured using the EORTC QLQ-C30 questionnaire. Secondary outcome measures include breathlessness and pain measured using a 100 mm Visual Analogue Scale and health-related QoL at 60 and 90 days. A sample size of 142 patients is needed to demonstrate a clinically significant difference of 8 points in global health status at 30 days, for an 80% power and a 5% significance level.

**Ethics and dissemination:**

The study has been approved by the NRES Committee South East Coast—Brighton and Sussex (reference 15/LO/1018). The trial results will be published in peer-reviewed journals and presented at scientific conferences.

**Trial registration numbers:**

UKCRN19615 and ISRCTN15503522; Pre-results.

Strengths and limitations of this studyThis is the first prospective randomised controlled trial primarily comparing quality of life (QoL) outcomes between inpatient and outpatient treatment pathways for malignant pleural effusion.The primary outcome measure is clinically relevant.Patients with non-expandable lung are also included in the study.The study represents real life presentation and management.A limitation is that patients with poor performance status are not included and only patients with potential for ambulatory management are included. However, to include those patient groups a separate study design to answer that specific question will have to be conducted.

## Introduction

Malignant pleural effusion (MPE) is a common presentation in advanced malignancy, complicating nearly 50% of all lung and breast cancers.^1^ Extrapolated data estimate 50 000 new cases of MPE per year in the UK, translating to one new case per 1000 population per year.^2^ MPE results in significant morbidity, including disabling breathlessness, pain and reduced physical capability. With advancement of techniques over the last decade, physicians and patients are faced with a number of choices in the management of MPE. These choices depend on many factors, and not all patients are suitable for every strategy. Regardless of the choice, the aim should be an overall improvement in quality of life (QoL).

Managing patients with an easily implemented ambulatory pathway which averts the need for an inpatient hospital stay may improve QoL in a population with an otherwise poor prognosis.^3^ To investigate this, the OPTIMUM trial, a National Institute for Health Research (NIHR) Portfolio multicentre study (UKCRN 19615), is currently open to taking on other recruiting sites.

### British Thoracic Society guidelines

The 2010 British Thoracic Society (BTS) pleural disease guideline advocates chest tube drainage and chemical pleurodesis involving a hospital admission.^4^ The sclerosant of choice in the UK is graded large-particle talc, a safe and effective sclerosant at a dose of 4 g.^4^ Median length of a hospital admission for this intervention is 4 days (IQR 2–6 days).^5^

### The indwelling pleural catheter

An alternative and increasingly popular strategy to manage MPE is the insertion of an indwelling pleural catheter (IPC) as an outpatient and continued management on an outpatient/ambulatory basis. The BTS recognises that IPCs are effective in controlling recurrent effusions and are particularly useful in cases of trapped lung, where talc pleurodesis is likely to fail. It is a safe procedure which can be managed in the outpatient setting, thus avoiding hospital admission.^6^

A relatively new treatment pathway involves instillation of talc via an IPC to prevent recurrence, allowing the opportunity to manage people as outpatients. This novel pathway in the management of MPE is well established at Guy's and St Thomas's Hospital. Our case series of 24 patients who underwent talc pleurodesis via an IPC confirms the safety and efficacy of this treatment algorithm^7^ on which the OPTIMUM trial is based.

A huge body of research has looked into the therapeutic management of MPE. This has led to multiple management pathways. However, there is no one definitive management strategy. Despite the goal of palliation, the majority of studies focus on outcome measures such as pleurodesis success rate, failure rate and complications.^6^
^8–12^ While this is important, we believe it is important to understand the impact of these interventions on the overall well-being of patients.

There is a paucity of data on QoL outcomes in this population, particularly the effects of different pleural interventions. A retrospective study of talc pleurodesis by surgical video-assisted thoracoscopy failed to show any QoL benefit at 3 and 6 months.^13^ The Second Therapeutic Intervention in Malignant Effusion (TIME2) randomised controlled trial showed no difference between medical pleurodesis and IPC insertion without talc in relieving breathlessness. Global QoL evaluated as a secondary measure did improve in both groups at 6 weeks, but there was no significant difference in QoL at any time point.^5^ There are no prospective randomised controlled trials primarily comparing QoL outcomes in the outpatient and inpatient management of MPE.

## Objectives

### Hypothesis

The primary hypothesis is that outpatient management of MPEs with an IPC improves global health-related QoL at 30 days following insertion when compared to standard treatment according to BTS guidelines.

With no validated QoL assessment tools for patients with MPE, global health-related QoL as measured by the EORTC QLQ-C30 has been selected as the primary outcome measure. It is an extensively used tool and validated for malignant disease of various histological types.^14^ Using one tool to assess health-related QoL will ensure that the protocol limits the burden to trial participants.

Primary and secondary objectives and outcome measures are summarised in table 1.

**Table 1 BMJOPEN2016012795TB1:** Primary and secondary objectives for the OPTIMUM trial

Objectives	Outcome measures	Time points of evaluation
*Primary objective*		
To assess whether a minimally invasive evidence-based pathway for the outpatient management of malignant pleural effusion improves global health-related quality of life at 30 days	Self-reported health-related quality of life based on EORTC QLQ-C30 questionnaire	Day 30
*Secondary objectives*		
Improvement in global health-related quality of life at 60 and 90 days	Self-reported health-related quality of life based on EORTC QLQ-C30 questionnaire	Day 60, 90
Pleurodesis failure rate	Subsequent pleural intervention required on the same side as pleurodesis Chest X-ray opacification greater than 25% on side of intervention judged by two independent clinicians	Day 30, 60, 90
Improvement in symptoms of pain and breathlessness	Medical Research Council (MRC) Dyspnoea Scale 100 mm Visual Analogue Scale for pain and breathlessness	Day 30, 60 and 90
Complication rate	Clinical review and adverse event documentation	Day 7, 14, 30, 60 and 90

## Methods and analysis

### Trial design

The OPTIMUM trial is a prospective, two-arm non-blinded randomised multicentre trial. The Medicines and Healthcare products Regulatory Agency have cleared this trial as a non-clinical trial of investigational medicinal product (non-CTIMP) study. All patients presenting to recruitment centres with MPEs who fulfil the inclusion criteria will be approached. The trial is currently open at eight sites in the UK: St Thomas' Hospital, London; King's College Hospital, London; Princess Royal Hospital, Bromley; East Surrey Hospital, Redhill; East Sussex Hospital, Eastbourne; St George's Hospital, London; Hull Royal Infirmary, Hull and Medway Maritime Hospital, Gillingham. At the time of publication, we are actively seeking more sites to recruit.

### Study population

A total of 142 patients in participating respiratory departments meeting the eligibility criteria will be recruited. All sites have a dedicated pleural service with experience in IPC insertion.

### Inclusion criteria

Diagnosis of MPE.^i^WHO performance status 2 or less unless performance status is impaired by the presence of effusion and likely to significantly improve with drainage.Expected survival <3 months.

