**Figure 2 BMJOPEN2016012795F2:**
[figure not shown]
Sites of thoracic ultrasound to assess for pleural apposition.

If the lung has not re-expanded, continued regular drainage (depending on fluid output) will be advised.

If talc pleurodesis is attempted based on the above criteria, this will be administered as a ‘slurry’ via the IPC. Then, 3 mg/kg (max 250 mg) 1% lignocaine will be instilled into the pleural space via the IPC to prevent any acute pain. This will be followed by 4 g of talc mixed with 50 mL normal saline via the drain followed by 50 mL normal saline flush. Patients will be observed for at least 1 hour following talc instillation.

The patient will then be sent home with the advice to drain daily with a 1 L vacuum bottle for 3 days. This can be performed by themselves, their carer or district nurse. They will be reviewed on the third day postpleurodesis (+48 hours). They will be asked to complete health-related QoL and symptom questionnaires and undergo ultrasound and chest X-ray review of the pleural collection.

If there is no recurrence of effusion with satisfactory ultrasound evidence of pleural symphysis in at least five out of six areas, patients will be advised not to undertake any drainage for further 7 days. On day 14 (±24 hours) postintervention, they will undergo QoL and symptom questionnaires, ultrasound and chest X-ray review. If pleurodesis is successful, the IPC will be removed.

Successful pleurodesis will be defined as pleural symphysis in at least five out of six areas (see figure 2) on ultrasound as evidenced by the absence of lung sliding in these areas.

Patients will undergo a clinic review at 30, 60 and 90 day's postprocedure. At each visit, a chest X-ray and chest ultrasound scan will be performed recording X-ray appearances and the presence of pleural thickening, depth of effusion and extent of septations on ultrasound. Patients will be required to complete the EORTC QLQ-C30 questionnaire, MRC Dyspnoea Scale and VAS for pain and breathlessness.

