**Figure 3 BMJOPEN2016012795F3:**
[figure not shown]
Trial pathway for the usual care group. CXR, chest X-ray; USS, ultrasound scan; IPC, indwelling pleural catheter; QoL, quality of life.

From day 2 to 5 patients will be assessed for complications, drain output and lung re-expansion. If clinically possible, any steroids will be discontinued. Once full lung re-expansion is confirmed on X-ray (defined as full re-expansion of the lung to the chest wall or only blunting of the costophrenic angle on the affected side), talc slurry will be performed.

If lung re-expansion is unsatisfactory with evidence of trapped lung on chest X-ray (<50% pleural apposition on chest X-ray), then pleurodesis will not be attempted and the drain removed with early follow-up of the patient to consider repeated drainage of the effusion or IPC insertion if symptomatic.

If pleurodesis is performed, it will be carried out as per the BTS guidelines. Then, 3 mg/kg (maximum 250 mg) of 1% lignocaine will be administered via the chest drain. This will be followed by 4 g talc mixed with 50 mL saline instilled through the drain, followed by 50 mL saline flush of the drain into the pleural cavity. The drain will be clamped and left closed for 1 hour. After this time, the drain will be opened and left on free drainage for 24–72 hours. If the fluid output is <250 mL per day, the drain will be removed and patient will be discharged home. Complications, drain output and the use of thoracic suction (which will be at the discretion of the treating team) will be recorded. If the output is high, the drain will be left longer and depending on the clinical assessment as per the standard practice, the drain will be removed.

Patients will have follow-up on the 7th day and 14th day postprocedure. During each follow-up, they will undergo a chest X-ray and chest ultrasound and be asked to complete the QoL and symptom questionnaires. They will also undergo the same assessment at follow-up 30, 60 and 90 days after the intervention. If the pleurodesis is not successful, they will have further assessment and will be managed based on clinical requirement regarding the need for further pleural intervention.

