### Data management

These data will be collected by the trial coordinator, principal investigators and research nurse. Patient data will be anonymised with trial number allocations. Data will be recorded on paper case report forms in booklets comprised of triplicate carbon copy paper. The data will be analysed by the clinical research fellow, the chief investigator and the trial statistician. This will primarily be performed at St Thomas' Hospital. This is an 18-month trial (total 3 months of follow-up) with subsequent data analysis and manuscript production. The VAS Score will be measured by two members of the trial team at the coordinating centre. Case Report Forms will be stored in locked filing cabinets. The completed case reports forms will undergo quality control assessment once the patient has completed or withdrawn from the trial by the trial coordinator and manager before transcription onto a password-protected database on a secure computer network. This will performed by two members of the trial team to ensure quality control and data reliability. As this is a non-CTIMP trial, a data monitoring committee is not required; however, the interim analysis will be performed by the trial statistician independent of the investigators.

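### The survival inclusion criterion, as printed, contradicts the 3-month follow-up and the day-90 (and to a lesser degree day-60) outcomes

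*Protocol article*

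**What the plan says.** The Inclusion criteria section of the Protocol article has three entries: the diagnosis, a performance-status limit, and "Expected survival <3 months".

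The rest of the article plans for patients who reach three months:

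- Table 1 (Objectives) has as a secondary objective "Improvement in global health-related quality of life at 60 and 90 days". It also sets pleurodesis failure, pain and breathlessness, and complications as outcomes at days 60 and 90.
- Table 2 (Study procedure) schedules the questionnaires, chest X-ray and thoracic ultrasound at days 30, 60 and 90 in both arms.
- For the catheter arm: "Patients will undergo a clinic review at 30, 60 and 90 day's postprocedure".
- For the usual care arm: "They will also undergo the same assessment at follow-up 30, 60 and 90 days after the intervention".
- Data management: "This is an 18-month trial (total 3 months of follow-up".

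The primary outcome comes earlier: "The primary outcome measure is global health-related QoL at 30 days measured using the EORTC QLQ-C30 questionnaire".

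**The concern.** An inclusion criterion decides who may enter. Taken as printed, this one makes a patient with an expected survival of three months or more ineligible. Those are the patients most likely to supply the day-90 data, and the best placed to supply the day-60 data. The entry rule and the outcome schedule therefore pull against each other.

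Two things are at stake. First, the later comparisons would rest on a subset selected by survival, with much of the randomised sample lost to death. Second, the Trial design section says that patients meeting the inclusion criteria will be approached, that eight sites are open and that more are sought. If one site applied the printed rule and another assumed the opposite inequality, they would recruit populations that hardly overlap in prognosis.

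**Working it through.** **Step 1. Timing.** Three months is about 91 days (3 × 30.44). A patient meeting the criterion is expected to die by about the day-90 visit. Only a patient expected to live under 60 days is expected to die before the day-60 visit, and only one expected to live under 30 days before the primary endpoint. The conflict is thus direct at day 90, partial at day 60 and weaker at day 30.

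**Step 2. Is it resolved elsewhere?** No other section qualifies or restates the survival criterion. The other inequalities nearby (the age exclusion and the age strata for randomisation) run in the expected direction, so there is no general fault with the symbols.

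**Step 3. Reproduce the planned sample size.** Inputs from Sample size calculation and statistical analysis: difference 8 points, SD 23.60, R² 0.49, 5% F test, 71 per arm.

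- Adjusted SD = 23.60 × √(1 − 0.49) = 16.85.
- Noncentrality at n per arm: λ = (n/2) × (8/16.85)² = (71/2) × 0.2253 = 8.00.
- Noncentral F with 1 and 2n − 3 = 139 degrees of freedom: power 0.802. At 70 per arm it is 0.796.

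So 71 per arm is reproduced. The number needed, 142, is also the randomisation target, so there is no allowance for death or other loss.

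**Step 4. Illustrate the truncation.** The documents give no survival distribution. Assumptions: exponential survival, S(t) = 0.5^(t/median); death is the only loss; deaths are equal between arms. Medians of 1.5 and 3 months are taken as 45 and 90 days. A 180-day median is added as a comparison.

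| Assumed median | Alive at day 30 | Day 60 | Day 90 | Of 142 (days 30/60/90) |
|---|---|---|---|---|
| 45 days | 63% | 40% | 25% | 89 / 56 / 36 |
| 90 days | 79% | 63% | 50% | 113 / 89 / 71 |
| 180 days | 89% | 79% | 71% | 127 / 113 / 100 |

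Counting a month as 30.44 days changes these by about one percentage point at most (for example 80% rather than 79% at day 30).

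**Step 5. Day-30 power if only survivors are analysed.** The formula is that of Step 3 with n = 71 × S(30).

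| Assumed median | n per arm | λ | Power |
|---|---|---|---|
| 45 days | 44.7 | 5.04 | 0.602 |
| 90 days | 56.4 | 6.35 | 0.705 |
| 180 days | 63.3 | 7.13 | 0.754 |

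**Step 6. Split the shortfall.** At a 180-day median the loss is already 0.802 − 0.754 = 0.048, because 142 has no allowance for death. The further loss from shorter survival is 0.754 − 0.705 = 0.049 at a 90-day median and 0.754 − 0.602 = 0.152 at a 45-day median.

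**The case against.** The other side accepts the textual conflict but limits what can be built on it. Most of its points stand.

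- **A reader might infer that the outcomes cannot be measured in this population.** That does not follow. The primary endpoint is at day 30, quality of life is also collected at days 7 and 14, and expected survival is a forecast that some patients outlive. At a 90-day median, 63% are alive at day 60 and half at day 90. The survivors are a minority at both visits only under the shorter assumed median.
- **A reader might infer that patients are expected to die before day 60.** The criterion sets the limit at about day 91, and a patient expected to live two to three months reaches day 60.
- **A reader might cite the performance-status text as a second contradiction.** The article says "A limitation is that patients with poor performance status are not included". But performance status is not a survival limit, the criterion itself has an exception ("WHO performance status 2 or less unless performance status is impaired by the presence of effusion"), and randomisation is stratified with a level for status 3. This adds little.
- **A reader might charge the whole power loss to the inequality.** Step 6 shows that part of it comes from the missing allowance for death, and all of it depends on an assumed distribution.
- **A reader might infer that sites have recruited the wrong patients, or that the sign is certainly a misprint.** Only the article is available. Sites may work from a full protocol worded differently, and the documents do not show which rule was intended.

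None of this removes the contradiction. The criterion is a positive statement of who may enter, not a detail that a condensed article leaves to a fuller document.

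**Conclusion.** The point holds as an internal contradiction: the printed survival criterion is at odds with the 3-month follow-up and the day-90 outcomes, and to a lesser degree with the day-60 outcomes. Confidence in that is high, because it rests on the text alone.

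The size of the consequence is illustrative. It rests on exponential survival, death as the only loss, equal deaths by arm, and medians that the documents do not give. On those assumptions a quarter to a half of patients would be alive at day 90, so the later comparisons would be heavily truncated by death. Day-30 power would be roughly 0.60 to 0.71, only part of that shortfall being due to the criterion.

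A reversed sign, or an exclusion criterion printed under inclusion, is a natural suspicion, but only the sponsor can confirm it. This review takes no position on which survival rule is right.

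**What to change.** The sponsor should reconcile the Inclusion criteria with the day-60 and day-90 objectives:

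1. Check the direction and the placement of the survival criterion against the approved protocol and the case report form.
2. Correct whichever text is wrong.
3. Notify current and prospective sites of the confirmed rule.
4. Check screened and enrolled patients against it, using the screening logs.
5. If the criterion is intended as printed, restate the day-60 and day-90 objectives and the power for that population.

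The cost depends on what step 1 finds. If only the article is wrong, it is a published correction, a notice to sites and a log check. If sites have screened to an unintended rule since enrolment began in July 2015, the review of enrolled patients is a larger task and may need an amendment. If the printed rule is intended, the cost is a revised set of later objectives and a new power calculation.

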### Exclusion criteria

Age <18 years old.Pregnant or lactating.Known allergy to talc or lignocaine.Lack of symptomatic relief from effusion drainage.District nurse/carers/hospital team unable to carry out at least twice weekly drainage from an IPC.Lymphoma or small cell carcinoma except:^ii^
Failure of chemotherapy.Deemed for palliative management.Non-malignant effusions.Loculated pleural effusion that would prevent successful drain insertion and clinical benefit to the patient.Unable to provide written informed consent to trial participation.

### Recruitment and randomisation

Enrolment started in July 2015 and is anticipated to continue until January 2020. In each centre, the trial team will screen patients presenting to the respiratory and oncology clinics as well as inpatient wards.

Once screening procedures have confirmed a patient's eligibility, they will be approached and consented for the study. They will undergo stratified randomisation (1:1) to either usual care as per BTS guidance or treatment with an IPC. This will be performed using a web-based secure randomisation service for clinical trials (http://www.sealedenvelope.com). The stratification variables are age (<65 years, ≥65 years), malignancy subtype (lung, mesothelioma, breast, other) and WHO performance status (0, 1, 2, 3). Given the nature of the intervention, patients and the research team will not be blinded.

